### Safety and ethical aspects of the trial

The trial procedures follow the Declaration of Helsinki and the ICH Guidelines for Good Clinical Practice (ICH-GCP) [51]. The Ethics Committee of the German Psychological Association (Deutsche Gesellschaft für Psychologie, DGPs) approved the study procedures (approval date: 6 May 2019). Modifications of the protocol, which are not merely of administrative nature, such as minor corrections or clarifications, and which might impact patient safety, ethical aspects of the trial or the conduct, and scientific evaluation of the trial, will be submitted as protocol amendments to the Ethics Committee and require approval. Furthermore, the record at the trial registry DRKS will be updated and the BMBF will be informed in case of protocol amendments. Such amendments will be agreed upon by the PI after consultation with the External Advisory Board.

### Safety aspects

So far, no trial has ever reported serious adverse events (SAEs) caused by psychotherapy of trauma-related disorders in children and adolescents [cf. 52, 53]. Since the planned treatment study can be, therefore, considered as safe, we refrain from installing an external Safety Monitoring Committee for pragmatic reasons. Instead, we have appointed a SAE Management Committee constituted of the lead investigators at the sites ([name], [name], [name], [name]), the PI ([name]), the independent biostatistician and the External Advisory Board of the trial who will supervise the safety of the study.

The following dangerous occurrences will be defined as SAEs in accordance to the ICH-GCP and will be closely monitored during treatment, and at the follow-up assessments:
Attempted suicideEvent which results in death (suicide or other)Life-threatening eventEvent which results in significant disability

All such dangerous events and other safety aspects will be forwarded to the SAE Management Committee. In addition, the independent biostatistician will conduct interim analyses after 30% and 50% of the completed 6-month follow-ups in order to monitor the symptom development as well as the occurrence of potential SAEs. If an SAE is identified, the SAE Management Committee will investigate whether there is a causal link between the trial and the SAE. If the SAE Management Committee decides that further trial participation would be a safety concern for the patient, the patient will be withdrawn from the study. In the case of serious safety concerns, the trial will be stopped.

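### No stated barrier keeps interim symptom and SAE results from the site leads and the PI, and SAEs are looked for more often in the KIDNET arm than under TAU

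*Protocol article*

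**What the plan says.** All of the monitoring rules stand in the Safety aspects section of the protocol article.

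- **Looks.** "the independent biostatistician will conduct interim analyses after 30% and 50% of the completed 6-month follow-ups in order to monitor the symptom development". The same looks also cover possible SAEs. PTSD symptom severity on the CAPS-CA-5 is the primary outcome (Primary outcome section).
- **Oversight.** "we refrain from installing an external Safety Monitoring Committee for pragmatic reasons". The replacement is "a SAE Management Committee constituted of the lead investigators at the sites", the PI, and "the independent biostatistician and the External Advisory Board of the trial who will supervise the safety of the study". The Discussion acknowledges that the trial is led by a developer of the therapy and that allegiance may count as a limitation.
- **Flow of information.** "All such dangerous events and other safety aspects will be forwarded to the SAE Management Committee". The committee judges causality and decides on withdrawal of individual participants; the trial can be stopped for serious safety concerns. No recipient of the interim analyses is named, nor whether they are split by arm.
- **SAE schedule.** SAEs "will be closely monitored during treatment, and at the follow-up assessments". The study delivers 11 KIDNET sessions, and continuous safety monitoring is one of the aims of session 1 (KIDNET section). TAU participants are referred to the regular health system, and the care they received is recorded only after each follow-up assessment (TAU section).
- **SAE list.** It has four entries: attempted suicide, death, a life-threatening event and significant disability. Acute risk needing inpatient treatment is an exclusion criterion at entry but is not on the list.

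**The concern.** There are two linked problems.

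First, the looks cover the primary outcome, and the biostatistician who runs them sits on a committee with the PI and every site lead. Nothing in the text keeps arm-level results from these colleagues. Participants and therapists are unblinded, and the treatment is delivered and supervised at the sites. Knowledge of the trend could affect recruitment effort, supervision and expectations for the participants still to come.

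Second, the SAE schedule gives the two arms different chances of having an event noticed. A reader of interim or final SAE counts by arm would be comparing frequent study contact with two interviews. That could suggest harm from KIDNET where there is none, or leave TAU events unseen, in the very data on which safety concerns are judged. The SAE list adds a smaller gap: an admission for acute risk after randomisation is not a listed category, although the same state is serious enough to bar entry.

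**Working it through.** **1. The plan's own figure.** Inputs from the power analysis section: d = 0.6, one-sided alpha 0.05, power 0.80, 1:1 allocation. A one-sided two-sample t-test needs 35.04 per arm, rounded up to 36, so N = 72, as stated. The planned enrolment is 80.

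**2. When the looks fall.** Inputs: 80 participants; recruitment from June 2019 to about May 2021 (Trial status), taken as 24 months; t2 at 6 months. Assumptions: even accrual, no loss, and the percentages refer to 80 follow-ups.

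- Accrual: 80 / 24 = 3.33 per month.
- First look: 0.30 × 80 = 24 follow-ups, at 24 / 3.33 + 6 = 13.2 months. Randomised by then: 13.2 × 3.33 = 44. Still to come: 80 − 44 = 36.
- Second look: 0.50 × 80 = 40 follow-ups, at 40 / 3.33 + 6 = 18 months. Randomised by then: 18 × 3.33 = 60. Still to come: 80 − 60 = 20.

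**3. Would an arm-level summary reveal the trend?** With N followed up in total, SE(d) is about √(4/N). If the true d is the planned 0.6, the chance that the observed difference favours KIDNET is Φ(0.6 / SE).

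| Look | N | SE(d) | Chance of pointing to KIDNET |
|---|---|---|---|
| First | 24 | 0.41 | 0.93 |
| Second | 40 | 0.32 | 0.97 |

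**4. Study contacts at which an SAE can be picked up, from the article's text.**

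| | KIDNET | TAU |
|---|---|---|
| Study sessions | 11 | 0 |
| Follow-up interviews | 2 | 2 |
| Total | 13 | 2 |

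At each look, 20 participants (44 − 24, then 60 − 40) are randomised but not yet at t2. If the SAE count covers everyone randomised so far, those of the 20 who are in KIDNET can contribute session-detected events, while those in TAU have had no scheduled study contact since baseline.

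**5. Size of the detection bias.** The capture rates are not in the document and are assumed here. With equal true risk, the apparent risk ratio (KIDNET over TAU) is 1 / (TAU capture relative to KIDNET). Expected counts use 40 per arm and an assumed true risk of 5% with full capture in KIDNET, so 40 × 0.05 = 2.0 events in KIDNET.

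| Relative TAU capture | Apparent risk ratio | Expected TAU events |
|---|---|---|
| 50% | 2.0 | 1.0 |
| 70% | 1.43 | 1.4 |
| 90% | 1.11 | 1.8 |

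**The case against.** The strongest reply is that this is a condensed article. Recipients and format of interim reports commonly sit in a full protocol or analysis plan, and protocol version 1.5 is not shown. That carries weight: silence about recipients, or the lack of a sentence excluding an efficacy stop, would not be a point on its own. But the article itself fixes the looks, their content, the committee's membership and the SAE schedule, and those elements together create the exposure.

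Several stronger readings are tempting and are not supported:

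- *The committee consists only of investigators.* It also includes the independent biostatistician and the External Advisory Board.
- *Interim results are sent to the committee.* The text forwards SAEs and other safety aspects to it and describes the interim analyses separately. That symptom results reach it is an inference. The Data management section limits access to the merged dataset to the data management team, but this does not cover interim output.
- *Outcome ratings are compromised.* Follow-up assessors are independent and blinded to allocation, unblinding is documented, 10% of interviews are re-rated, and allocation is concealed with varying, undisclosed block sizes. Nothing says that site leads see later ratings.
- *A planned SAE comparison is biased.* No formal comparison by arm is specified; the text describes case-by-case causality review. The likely bias would also run against KIDNET, not for it.
- *The looks inflate the type I error.* Unadjusted one-sided 0.05 tests at 30%, 50% and 100% of the information would give about 0.103 overall, but the plan states no interim efficacy test. The figure is conditional on testing that is not planned.

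It is also fair to note that both arms already receive the same suicidality and self-injury items at t2 and t3 and a medical history at each interview, so part of an equal assessment is in place. The legend of the SPIRIT figure lists (S)AE, so the figure, which was not available here, may show more on safety timing. Closer watching during exposure sessions is a proper safeguard; the difficulty lies only in comparing its yield with TAU. Finally, an entry criterion does not define an SAE, and admissions might reach the committee as other safety aspects. The text does not say that they will.

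**Conclusion.** The point holds in a limited form and is worth a protocol change. As written, nothing separates interim arm-level results from the PI and site leads, and SAE capture differs by arm because only KIDNET has study sessions.

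On size: at the looks about 36 and then 20 of 80 participants remain to be randomised, assuming even accrual over 24 months and no loss. If d is 0.6, an arm-level summary would point towards KIDNET with probability about 0.93 and 0.97. Whether investigators would see such a summary is not stated; the documents support only that they may. An apparent SAE ratio of 1.11 to 2.0 under equal true risk rests wholly on assumed relative capture of 90% to 50%, and with about two expected events per arm it would be a matter of one event or less. The gap in the SAE list is a point to reconcile, not evidence that admissions will be lost. No inflation of the type I error follows from the plan as stated.

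**What to change.** 1. **Interim results.** State that arm-level results go only to the independent biostatistician and the existing External Advisory Board. The PI and site leads receive a recommendation, plus individual SAE cases for causality review.
2. **Purpose of the looks.** State that they serve harm monitoring and involve no test of efficacy.
3. **SAE summaries by arm.** Base any between-arm summary, interim or final, on one structured set of questions asked identically at t2 and t3 in both arms. List events detected at KIDNET sessions separately. Monitoring during sessions stays as it is.
4. **Inpatient admission.** Record it in both arms as a reported safety event, and reconcile the SAE list with the exclusion criterion on acute risk.

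The cost is a few sentences of protocol wording and one form. No new committee or staff is needed, since the Advisory Board already exists. The real price is that the PI and site leads give up direct sight of arm-level interim data.

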## Methods

### Trial design

YOURTREAT is a randomized controlled, rater-blinded, two-arm, multi-center, superiority trial with a 1:1 allocation ratio to two parallel groups. Individuals who are screened eligible for the trial will participate in a comprehensive diagnostic interview (t_1_). Among other information (detailed below), this structured interview will assess the diagnosis of PTSD according to the *Diagnostic and Statistical Manual of Mental Disorders, 5th edition* (*DSM-5*). We expect that we will have to interview approximately *N* = 220 children and adolescents (*N* = 55 per site) in order to identify 80 participants (*N* = 20 per site) who fulfill the diagnostic criteria of PTSD. These PTSD patients will be immediately randomized to one of the two arms of the trial; KIDNET or TAU. For individuals included in the KIDNET group, the treatment starts within 1 month after the diagnostic interview and should be terminated at the latest 5 months after randomization. For the beginning and ending of the NET, a tolerance window of 1 week is considered acceptable. Deviations from this time window will be reported. Individuals assigned to TAU will be informed about treatment and counseling options within the local general health care system immediately after the diagnostic interview.

Six months after the diagnostic interview and the randomized group allocation, the first follow-up interview will take place (t_2_). This time point was selected in order to assure a minimum time interval of 1 month between the end of KIDNET and the first follow-up interview. In this way, the diagnostic interview which measures PTSD symptoms in the past month, will not be biased by the experience of symptoms during exposure therapy. The second follow-up interview (t_3_) is scheduled for 12 months after randomization. For the appointments of the follow-up interviews, a tolerance window of ±  2 weeks is considered acceptable. Deviations from this time window will be reported. See Fig. 1 for a schematic overview of the participant flow through the trial. The study protocol was written following the Standard Protocol Items: Recommendations for Interventional Trials (SPIRIT) Statement 2013 [32]. See Additional file 1 for the SPIRIT Checklist. The trial was registered at the German Clinical Trials Registry (Deutsches Register Klinischer Studien; DRKS) on 15 May 2019 (ID: DRKS00017222).

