#### Treatment as usual (TAU)

Children and adolescents allocated to the TAU group will be referred to the local regular health care system for treatment. Immediately after the communication of group allocation, they will receive detailed information on how to find psychotherapeutic support in their community. For children under the age of 16 years, the psychoeducation on how to find psychotherapeutic support in the community will take place in the presence of the parent or guardian. The interventions provided to the TAU group will be assessed after each follow-up diagnostic assessment.

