### Data analyses

The confirmatory analysis of this study will be calculated as a mixed-effects model with the CAPS-CA-5 score as the outcome variable. Mixed models are especially suited for longitudinal studies as they can account for serial correlation within participants, are relatively robust to randomly missing data, and can incorporate certain nonrandom missing data without biasing model estimates. In detail, participants will be modeled as a random factor (including random intercepts or random intercepts and slopes), while time and intervention (KIDNET vs. TAU), as well their interaction, will be modeled as fixed factors. The hypothesis that KIDNET is superior to TAU in the treatment of PTSD will be evaluated by the significance test of the interaction effect time × intervention.

In case of a significant interaction effect, two planned general linear hypotheses will be calculated as post-hoc tests for linear mixed-effect models in order to test between-group differences at t_2_ and t_3_. One-sided *p* values will be adjusted for multiple comparisons following the Holm procedure.

We will perform an intention-to-treat analysis; that is, all trial participants will be analyzed as randomized, even if they discontinue treatment or are unavailable for one or both of the follow-up interviews. The between-group effect size (Cohen’s *d*) will be calculated at each follow-up assessment (t_2_ and t_3_). The intention-to-treat analysis will be supplemented by a modified intention-to-treat analysis which will include only those participants who participated in at least one post-randomization diagnostic interview. Furthermore, participants who were randomized to KIDNET will be included only if they participated in at least one KIDNET therapy session.

Continuous secondary outcome measures are analyzed in the same way. In the absence of a valid cut-off score for clinically significant change or treatment response of the CAPS-CA-5, the rate of subjects with clinically significant improvement as well as worsening based on the RCI will be compared between groups using Fisher’s exact tests at the follow-up assessments t_2_ and t_3_, separately. For this purpose, the RCI will be calculated based on the pre-treatment scores of the study sample following the suggestion of Jacobson and Truax [39]. Missing values due to premature withdraw will be considered as treatment failure (classified as no response).

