### Coping with distress

Similar to the re-experiencing symptoms that PTSD patients experience in everyday life, patients might also experience high and distressing levels of anxiety or other unpleasant emotional reactions during assessments or sessions of exposure-based psychotherapy. However, in contrast to their everyday experience, where they usually have to deal with these symptoms on their own, the assessor/therapist can help them to cope with these reactions, e.g., by reinforcing reality or by providing psychoeducation.

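### The safety rule names only withdrawal from the study, so stopping KIDNET for safety would also end that patient's t2, t3 and scheduled SAE recording

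*Protocol article*

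**What the plan says.** All references are to the protocol article.

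- **Safety aspects.** The SAE Management Committee reviews each SAE. If it decides that "further trial participation would be a safety concern for the patient, the patient will be withdrawn from the study", that is the action taken. The only other action named is stopping the whole trial. SAEs "will be closely monitored during treatment, and at the follow-up assessments".
- **Trial design.** In the KIDNET arm "the treatment starts within 1 month after the diagnostic interview and should be terminated at the latest 5 months after randomization". The follow-up interviews t2 and t3 are at 6 and 12 months.
- **Coping with distress.** Distress is foreseen "during assessments or sessions of exposure-based psychotherapy", so interviews and therapy are recognised as separate sources.
- **Data analyses.** Under intention-to-treat, "all trial participants will be analyzed as randomized, even if they discontinue treatment or are unavailable for one or both of the follow-up interviews". The modified intention-to-treat set requires at least one interview after randomisation. In the responder analysis, values missing through premature withdrawal count as treatment failure. Mixed models are said to be ones that "can incorporate certain nonrandom missing data without biasing model estimates".

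**The concern.** Trial participation has two parts: the therapy and the interviews. The article keeps them apart when it describes distress and when it lists what may happen to participants in the analysis. The patient-level safety rule does not. If the committee concludes that exposure sessions are harming a patient, the one action it is given also ends the interviews.

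The patients affected would be those for whom KIDNET may have done harm. Their later CAPS-CA-5 and C-SSRS scores would be missing for a reason linked to outcome. They would also leave both points at which SAEs are scheduled to be recorded. A patient withdrawn before t2 has no follow-up score for the interim looks at symptom development either. Harm data from the KIDNET arm would therefore be thinnest where they matter most.

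**Working it through.** **1. What the text fixes.** Safety aspects names two actions: withdraw the patient from the study, or stop the trial. No other section adds a treatment-only stop for safety. The intention-to-treat sentence foresees people who discontinue treatment, but it governs how they are analysed. It does not say that a patient stopped for safety keeps attending.

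**2. Timing.** KIDNET ends by month 5, with a 1-week tolerance. t2 is at month 6, with a tolerance of 2 weeks either way. Even at the edges of both windows, KIDNET ends before t2. A withdrawal during therapy that keeps to schedule therefore loses both t2 and t3.

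**3. Interviews lost.** Scheduled follow-up interviews: 80 × 2 = 160. One such withdrawal loses 2/160 = 1.25%. With no interview after randomisation, the patient also leaves the modified intention-to-treat set.

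**4. The plan's own figure, for context.** For d = 0.6, one-sided alpha 0.05 and power 0.8, the t-test needs 35.04 per arm. Rounded up to 36, this gives 72 in total, as stated. With 40 per arm the power is 0.845. With one KIDNET patient lost it is 0.841. Power is not the issue.

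**5. Shift in the contrast.** Inputs:
- 40 per arm (from N = 80 and 1:1 allocation).
- *gap*: how much worse the withdrawn patient's follow-up score would be than the mean of the other 39. Assumed 1 to 2 SD.
- *gap1*: the same excess at baseline. Assumed 0, then 0.5 SD.
- ρ: correlation between visits. Assumed 0.5.
- The patient would otherwise have attended t2 and t3.

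With complete data the arm mean at follow-up exceeds the mean of the other 39 by gap/40. With t2 and t3 missing, a random-intercept model predicts the patient from baseline only, so the excess becomes ρ·gap1/40. The shift is the difference:

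shift = (gap − ρ·gap1)/40, in favour of KIDNET.

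| gap (SD) | gap1 = 0 | gap1 = 0.5, ρ = 0.5 |
|---|---|---|
| 1 | 1/40 = 0.025 | (1 − 0.25)/40 = 0.019 |
| 1.5 | 1.5/40 = 0.0375 | (1.5 − 0.25)/40 = 0.031 |
| 2 | 2/40 = 0.05 | (2 − 0.25)/40 = 0.044 |

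The range is about 0.02 to 0.05 SD at both t2 and t3. With gap1 = 0, the shift is 0.025/0.6 = 4% to 0.05/0.6 = 8% of the planned d. The standard error of a simple standardised contrast is √(2/40) = 0.22, so the shift is about 11% to 22% of one standard error.

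**6. How often.** No SAE or withdrawal rate is given. At assumed rates of 1% to 5% per participant, an arm of 40 would see 40 × 0.01 = 0.4 to 40 × 0.05 = 2 such withdrawals. The upper end is generous: 5% is the ceiling that the sample size section cites for loss to follow-up in earlier NET studies. The shift in step 5 is per withdrawal.

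**The case against.** The strongest reply is that the rule fits its own trigger. It acts only when trial participation is unsafe, and participation includes the interviews. A concern about the sessions alone may not meet the trigger, and nothing forbids the committee from simply stopping therapy. The last part stands: the text does not prohibit a treatment-only stop. But it names no such step, and a committee following the text has only one patient-level action.

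A second reply is that the detail may sit in the full protocol, which is not shown. That is possible, and then only alignment is needed. The point is not a mere omission, however, because the article states a rule and the rule is broader than the concern it may be answering.

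Third, the size is an upper bound. Some patients after an SAE could not or would not be interviewed. The event that triggers review is already on record, so only later events are at stake. In the responder analysis the withdrawal counts against KIDNET, the opposite direction to the mixed model. All of this stands. The responder rule does not, however, alter the CAPS-CA-5 contrast.

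A reader might infer two stronger points that the article does not support.
- *That the rule contradicts intention-to-treat.* It does not: the patient is still analysed as randomised, with fewer data.
- *That the same loss arises in TAU.* There, "Children and adolescents allocated to the TAU group will be referred to the local regular health care system for treatment", so the trial delivers no therapy to stop. A judgement that participation is unsafe in that arm can concern only interviews and study contact, for which withdrawal is the right response. The record of TAU care would end as well ("The interventions provided to the TAU group will be assessed after each follow-up diagnostic assessment"), but a treatment-only stop would not recover it.

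**Conclusion.** The point holds for the KIDNET arm, as a cheap improvement and with medium confidence. As written, the safety rule turns a concern about therapy into loss of all remaining follow-up for that patient. The statement that mixed models tolerate some non-random missingness does not remove the problem: the model can borrow only from the baseline score, and it recovers nothing of a deterioration that happened afterwards.

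The loss is small: per withdrawal before t2, 2 of 160 interviews and at most about 0.02 to 0.05 SD in favour of KIDNET. This rests on an assumed gap of 1 to 2 SD, 40 per arm and full attendance otherwise. It would not by itself change the trial's conclusion, and the sample size stands. The stronger reason to act is the harm record, since later SAEs and suicidality scores would be lost for patients whose therapy was stopped because of possible harm.

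**What to change.** Reword the patient-level rule in Safety aspects along these lines:

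> If the SAE Management Committee decides that continued KIDNET is a safety concern for the patient, KIDNET will be stopped. t2, t3 and SAE recording continue if the participant (and guardian, where required) agrees and the committee judges the interviews safe. If the interviews are also a safety concern, the patient is withdrawn from the study.

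Stopping KIDNET stays mandatory, so protection is not weakened, and continued interviews depend on agreement and on the committee's judgement. Report KIDNET stops and study withdrawals by arm. If the full protocol already provides for a treatment-only stop, align the article's wording with it.

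The cost is a small amendment through the ethics committee, with the registry update and notice to the funder that the article requires for amendments. No visits are added. The downside is a few interviews with distressed participants, which the committee can waive.
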